# Duration of Protection From Pneumonia After Pneumococcal Vaccination in Hemodialysis Patients (DOPPIO): Protocol for a Prospective Multicenter Study

**DOI:** 10.2196/45712

**Published:** 2023-07-12

**Keywords:** Streptococcus pneumoniae, pneumococcal, vaccination, hemodialysis, clinical trial, vaccine, pulmonary, pneumonia, infectious disease, communicable disease, dialysis, kidney

## Abstract

**Background:**

Pneumonia is a leading cause of death in patients with end-stage chronic kidney disease treated with dialysis. Current vaccination schedules recommend pneumococcal vaccination. However, this schedule disregards findings of rapid titer decline in adult hemodialysis patients after 12 months.

**Objective:**

The primary objective is to compare pneumonia rates between recently vaccinated patients and patients vaccinated more than 2 years ago. As an exploratory objective, antipneumococcal antibody titers in hemodialysis patients will be determined as a function. Factors influencing antibody kinetics will be identified.

**Methods:**

Within this prospective multicenter study, we aim to compare 2 strata of vaccinated patients: those recently vaccinated and those vaccinated more than 2 years ago. A total of 792 patients will be enrolled. Twelve partner sites (within the German Centre for Infection Research [DZIF]) with allocated dialysis practices participate in this study. All dialysis patients who are vaccinated against pneumococcal infection in accordance with Robert Koch Institute guidelines prior to enrollment will be eligible. Data on baseline demographics, vaccination history, and underlying disease will be assessed. Pneumococcal antibody titers will be determined at baseline and every 3 months for 2 years. DZIF clinical trial units coordinate titer assessment schedules and actively follow-up on study patients for 2-5 years after enrollment, including validation of end points of hospitalization, pneumonia, and death.

**Results:**

The study has enrolled 792 patients and the last follow-up has been completed. Currently, the statistical and laboratory analyses are ongoing.

**Conclusions:**

Results will increase physician adherence to current recommendations. Establishing a framework for the efficient evaluation of guideline recommendations through a combination of routine and study data will inform the evidence base for future guidelines.

**Trial Registration:**

ClinicalTrials.gov NCT03350425; https://clinicaltrials.gov/ct2/show/NCT03350425

**International Registered Report Identifier (IRRID):**

DERR1-10.2196/45712

## Introduction

### Background

The global burden of disease continues to shift from acute communicable to chronic noncommunicable diseases and from years of life lost to years lived with disability [1]. Advanced chronic kidney disease (CKD; stages 3, 4, and 5 out of 5) is among the most common chronic health conditions in Germany [2]. Among CKD 5D (chronic kidney disease stage 5 with an indication for dialysis) patients, acute infections remain a leading cause of morbidity, mortality, and costs [3]. The most common infectious disease in CKD 5D patients is vaccine-preventable pneumonia. Recommendations in current vaccination guidelines acknowledge this substantial risk [4,5].

Observational studies suggest that pneumococcal vaccines lower mortality and morbidity in CKD 5D patients [6,7]. While a recent meta-analysis demonstrated the efficacy of pneumococcal vaccination in reducing pneumonia in the overall adult target population [8], randomized or well-designed prospective studies in a hemodialysis population are still lacking. Prior immunological studies in hemodialysis patients have been limited by low patient numbers and mixed populations (CKD 1-4, hemodialysis, and renal transplant recipients) [9]. While these studies suggest good immunogenicity of the vaccines, no attempts were made to verify the relevance of titers toward clinical end points in this population.

Current vaccination schedules recommend pneumococcal vaccination for patients older than 60 years or at increased risk for invasive pneumococcal disease every 6 years [4,5]. However, this schedule ignores preliminary findings of rapid titer decline in hemodialysis patients. Specifically, titers seem to decline substantially after 6 to 12 months in adult dialysis patients [10]. A limited number of studies with a longer follow-up period suggest a possible benefit of revaccination after 2 years [11,12].

### Scientific Rationale

Pneumonia is a leading cause of death in patients with end-stage chronic kidney disease (stage 5) treated with dialysis (CKD 5D). Acknowledging that many infectious complications are vaccine-preventable, specific recommendations have been issued for patients at risk.

In CKD 5D patients, these recommendations are based on weak evidence, namely immunologic studies [9] demonstrating the induction of antibody production and retrospective cohorts compare vaccinated to unvaccinated patients. Until today, not a single prospective study demonstrating a clinical benefit of pneumococcal vaccination in hemodialysis patients has been published. Furthermore, the aforementioned immunological studies suggest a rapid decline of protective antibodies in such patients, calling the current Robert Koch Institute (RKI) recommendation of vaccinating every 6 years into question.

While further research into the efficacy of pneumococcal vaccinations in hemodialysis patients is required, withholding vaccines would be unethical. However, comparing vaccinated patients to patients unwilling or unable to be vaccinated is likely to be a biased approach. We will thus compare 2 strata of vaccinated patients—those recently vaccinated and those vaccinated more than 2 years ago—concerning their protective antibody titers and their rates of pneumonia. We hypothesize that patients vaccinated more than 2 years ago, while in line with the current recommendation, no longer possess sufficient antibody response (<0.35 µg/mL serotype-specific IgG as defined in the World Health Organization [WHO] recommendation [13]) and thus have a risk of pneumonia comparable to an unvaccinated patient. Simultaneously, we will analyze titers of protective antibodies over time and identify factors predicting a more rapid decline.

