Participating sites will screen all hemodialysis patients at their outpatient dialysis clinic for eligibility. Eligible patients will be approached and informed by their physicians. If a patient agrees to participate in the study and signs an informed consent form (ICF), basic data regarding vaccination history, underlying disease, and so on will be entered or imported electronically into the study eCRF. Pneumococcal antibody titers will be drawn at baseline and every 3 months. For newly vaccinated patients, baseline titers will be drawn 4 weeks after vaccination. Deutsches Zentrum für Infektionsforschung (DZIF; English: German Center for Infection Research) clinical trial units (CTUs) will coordinate titer assessment schedules and inform the participating physicians of upcoming blood samplings. The samples will be taken on dialysis days from an already inserted-intravascular catheter. DZIF CTUs will actively follow up on study patients for 2-5 years after enrollment. This follow-up will include validation of all hospitalizations and deaths documented in the electronic registry to assess whether the primary end point (all-cause pneumonia) occurred. During months 25-30, only the primary end point will be recorded (ie, no blood samples will be taken). Additionally, dialysis units will be contacted every 6 months to assess if pneumonia occurred that did not require hospitalization. Blood samples will be stored frozen at DZIF CTUs, and titers will be analyzed at the end of this study. All therapies and diagnostics, including vaccinations, will be administered solely as part of the clinical routine and as recommended by appropriate guidelines (eg, RKI Ständige Impfkommission [STIKO] recommendations). Thus, Arzneimittelgesetz (AMG) does not apply to this study, and participating physicians do not require Good Clinical Practice (GCP) certification.

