### Data Collection

Study nurses will enter data into the eCRF either directly or by transfer of an extract from the patient’s electronic registry file (Qualität in der Nephrologie [QiN]; English: Quality in Nephrology database). The registry will also alert the study nurse to events during follow-up such as hospitalization, death, and transfer out of the dialysis unit, which are reliably captured because they are needed for billing purposes.

The central data repository will be the eCRF. Source documents will be stored in each patient’s study file.

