In general, immunological studies in hemodialysis patients have been carried out with limited patient numbers and in mixed populations (CKD, hemodialysis, and renal transplant recipients) [9]. Most studies suggest good initial immunogenicity, but titers seem to significantly decline after 6 to 12 months in adult dialysis patients [10]. The limited number of studies with longer follow-up periods suggests a possible benefit of revaccination after 2 years [11,12].

For the purpose of this calculation, we assume protection from pneumonia in the first 2 years to be equal to the protection recently demonstrated in an adult immunocompetent target population (relative risk 0.72) and afterward return to baseline. Thus, expected rates of pneumonia are 29.0/100 py in patients vaccinated >2 years ago and 20.88/100 py in patients vaccinated <2 years ago, respectively. To demonstrate the superiority of a more recent vaccination in preventing pneumonia with α=.05 and (1–β)=0.80, we would thus require 2 groups of 442 patients each (884 patients overall). Furthermore, the rate of pneumonia is also likely to be greater in an underprotected population than seen in the overall hemodialysis population, which includes a relevant number of freshly vaccinated patients. Additionally, the possibility of an unbalanced distribution of recently vaccinated patients (in a ratio of up to 1:7) was considered. A first statistical analysis will be discussed in an interim study report after 18 months.

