### Study Conduct and Statistical Analyses

The primary objective of this study is to compare pneumonia rates and outcomes between both groups. To achieve this, the raw number of events and raw rates of events per 100 patient years will be computed. For each group, the mean, median, SD, IQR, and minimum and maximum of demographical variables like age and sex will be computed. These observed variables will be used to build a Cox proportional hazard model. If applicable, this model will incorporate time-varying covariates and consider recurring events. To quantify the expected protective effect of a high titer level, multiple functional relationships will be explored, including but not limited to linear, quadratic, and step functions. Step functions will be created by dividing the titer levels into 10 mutually exclusive strata and estimating each risk individually. If possible, the largest difference between 2 neighboring strata will be identified as a threshold for an adequate titer level.

The secondary objectives of this study are to describe antibody titers as a function of time and factors influencing antibody kinetics. Descriptive statistics for titer levels at all intervals will be computed for absolute values as well as relative values (relative to the first observed or personal maximum). Levels for patients grouped by age, sex, and other variables of interest will be calculated. To allow a comparison, the mean, median, SD, IQR, and minimum and maximum titer levels will be calculated.

To identify which factors influence the absolute antibody titer level, multiple multivariate models will be built. In patients with available titers, risk factors for insufficient protection will be determined by multiple regression analyses of data including vaccination history and timing, medication exposure since last vaccination, history of underlying kidney disorder, dialysis, and demographic factors.

The titer levels will be assessed graphically by comparing boxplots of the titer levels at different time intervals. Concurrent titer levels will be tested for statistically significant differences by using a *t* test or a Mann-Whitney U test, whichever is applicable.

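### The two vaccination strata can differ in prior survival, dialysis vintage and frailty, and neither the demographic Cox model nor the stated limitations deal with this

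*Protocol article*

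**What the plan says.** Scientific Rationale rejects a comparison with unvaccinated patients as likely to be biased and replaces it: "We will thus compare 2 strata of vaccinated patients", one recent and one more than 2 years from the dose. Under Study Design, "Participating sites will screen all hemodialysis patients at their outpatient dialysis clinic for eligibility", and vaccination must precede enrollment. Inclusion Criteria ask for chronic hemodialysis at entry and say nothing about dialysis status when the dose was given.

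Study Procedure sizes the study on the statement that "expected rates of pneumonia are 29.0/100 py in patients vaccinated >2 years ago and 20.88/100 py in patients vaccinated <2 years ago", so the whole ratio of 0.72 is credited to vaccine protection. For the primary comparison, Study Conduct and Statistical Analyses first names demographic variables, with age and sex as examples, and continues: "These observed variables will be used to build a Cox proportional hazard model". Time-varying covariates and recurrent events are allowed if applicable, and a region of common support is required for the factors used.

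Limitations lists the pandemic, the missing pathogen data and the single-country setting. Conclusions says the comparison may estimate how long protection lasts.

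**The concern.** Choosing two vaccinated strata removes the bias of vaccine refusal but not every difference between the groups. Membership of the >2-year stratum is conditional on more than 2 years of survival after the dose. Membership of the recent stratum is not. The article itself calls pneumonia a leading cause of death in these patients, so the process that removes people before enrollment is plausibly tied to the primary endpoint. If the patients most prone to pneumonia are under-represented in the >2-year stratum, its rate is too low and real waning is understated. Age and sex capture little of this, and a common-support check covers measured factors only.

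At stake is the reading of the main result. A ratio near 1 could be taken as support for the 6-year schedule that the study questions, when it might partly reflect who was still alive to be enrolled.

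**Working it through.** **1. The plan's own figures.** These reproduce, so the point is not an arithmetic error.
- Original size, "with α=.05 and (1–β)=0.80", treating the rates as one-year risks, two-sided, unpooled variance: n = (1.960 + 0.842)² × (0.29×0.71 + 0.2088×0.7912) / (0.29 − 0.2088)² = 7.849 × 0.3711 / 0.006593 ≈ 442 per group, as stated. A pooled variance gives 445.
- Amended design (Amendment After Interim Study Report): 792 patients at 1:5 gives 132 and 660, followed for 2.5 years. Expected events are 132×2.5×0.29 = 95.7 and 660×2.5×0.2088 = 344.5. SE of the log rate ratio = √(1/95.7 + 1/344.5) = 0.1156. z = 0.3285/0.1156 = 2.84. Power = Φ(2.84 − 1.96) = 0.811, against 0.81 stated.

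**2. How much selection matters.** Let selection multiply the >2-year rate by q, with a true ratio of 0.72. The observed ratio is 0.72/q and the >2-year events are 95.7q. For q = 0.90: events 86.1, SE 0.1205, z = ln(0.90/0.72)/0.1205 = 1.85, power 0.46.

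| q | Observed ratio | Power |
|---|---|---|
| 1.00 | 0.72 | 0.81 |
| 0.95 | 0.76 | 0.65 |
| 0.90 | 0.80 | 0.46 |
| 0.80 | 0.90 | 0.13 |

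**3. Upper-end scenario, selection running from the dose.** Assumptions, none in the documents: mortality μ = 10-20% a year; gamma frailty with mean 1 and variance θ = 0.5-1.0; a share of one half to all of the death hazard carrying the same frailty as pneumonia; time since dose at entry uniform on 0-2 years (recent) and 2-6 years (comparator); 2.5 years of follow-up. Survivors at time s after the dose have mean frailty 1/(1 + ks), with k = θ × μ × share, from 0.025 to 0.2. Mean times since dose during follow-up are 1 + 1.25 = 2.25 and 4 + 1.25 = 5.25 years, so with no waning the recent/comparator ratio is about (1 + 5.25k)/(1 + 2.25k).
- k = 0.025: 1.131/1.056 = 1.07
- k = 0.1: 1.525/1.225 = 1.24
- k = 0.2: 2.05/1.45 = 1.41 (1.42 with person-time weighted by survival)

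Multiplying by 0.72, a true 0.72 would appear as 0.77 to 1.02.

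**4. Lower end, clock running from dialysis start.** A prevalent cohort was simulated with assumed vintage uniform on 0-10 years, frailty variance 0.5-1.0 and frailty-driven mortality of 15-20% a year. If dose date is unrelated to vintage, the frailty ratio between strata is 1.00. If doses are given only after dialysis starts, the crude ratio is 1.21-1.48, but about 1.00 among patients of the same vintage.

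**5. What a stratum term achieves.** Many patients enrolled as recent pass 2 years during follow-up. With uniform entry, 660 of them give 660 py before and 990 py after the 2-year point: 137.8 and 287.1 events, SE 0.104, z 3.17, power 0.89. If all entered at the dose, power is 0.79. Depletion continues after entry, however. Mean times since dose are 1.33 and 2.86 years, so under step 3 the no-effect ratio is (1 + 2.86k)/(1 + 1.33k), from 1.04 to 1.24 (about 1.25 at most).

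**The case against.** The best counter-argument is that step 3 starts the clock in the wrong place. Both strata are prevalent patients who survived to enrollment. Someone 5 years on dialysis and vaccinated last year has been through as much selection as someone vaccinated 3 years ago. Step 4 bears this out: the difference may vanish, or reduce to confounding by vintage, which can be measured. This stands, and it is why the range in step 3 is only an upper-end scenario.

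It is also fair that the covariate wording is open-ended, that the Explorative Objectives look at underlying disease and prior hospitalizations in relation to pneumonia, that the titer regressions use dialysis and kidney history, and that a fuller covariate list may sit in documents not shown. What the article does state for the primary model is a demographic basis, and its Limitations and Conclusions carry no caveat.

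A reader might infer three stronger claims, which the documents do not support.
- That >2-year patients had to stay on dialysis for 2 years after the dose. Only hemodialysis at enrollment is required, and the dose may precede dialysis.
- That selection is shown to mimic waning. Every ratio computed from depletion goes the other way. Transplantation of fitter patients or sicker patients not being revaccinated could push towards apparent waning, but nothing in the documents sizes that. A >2-year rate raised by 20-30% would give a spurious significant result 32-60% of the time, but that is a what-if.
- That a separate stratum term removes the bias. Step 5 shows that it does not.

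**Conclusion.** The point stands in limited form. The strata are non-randomised and differ in the survival needed to enter them, the primary model as described does not deal with the resulting differences in vintage and frailty, and the article does not acknowledge them. The size is not known. It runs from near zero, if dose timing is unrelated to vintage, to a true 0.72 appearing as 0.77-1.02 under the assumed mortality, frailty and dose-based clock. It would be wrong to conclude that the bias is as large as the effect sought: that needs the extreme of all three frailty assumptions at once. The net sign is uncertain. Even so, a 10% distortion of the >2-year rate takes power from 0.81 to 0.46, so the comparison needs a check on selection before it is read as duration of protection.

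**What to change.** 1. **Negative control.** Run the same between-strata model on non-pneumonia hospitalizations, specified before the strata are compared. Registry hospitalizations are described as events "which are reliably captured because they are needed for billing purposes", and Study Design already has the trial units validate all of them. If the strata differ there, limit the waning conclusion. A null result would not prove the absence of selection, as the article gives no hospitalization rate from which to judge its power.
2. **Adjustment.** Adjust the primary model for dialysis vintage, underlying disease and prior hospitalizations where recorded, not only for demographics.
3. **Sensitivity analysis only.** Add enrollment stratum as a fixed term beside a time-updated <2 / ≥2-year term, plus calendar period. State that this reduces but does not remove depletion bias (residual no-effect ratio about 1.04-1.25 under the same assumptions) and that its power is about 0.79-0.89 before that bias.
4. **Limitation.** List between-stratum selection, and word the conclusion on duration of protection to match.

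Enrollment and follow-up are complete and analysis is ongoing, so the cost is analyst time on existing data. Adjustment may lose some precision, and patients with missing vintage or history will need handling. Anything added after the strata have been compared should be labelled post hoc.

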### Objectives

#### Primary Objective

The primary objective is to compare pneumonia rates between newly vaccinated hemodialysis patients and those vaccinated against pneumococcal infection more than 2 years ago.

#### Explorative Objectives

The explorative objectives are as follows:

To describe the pneumococcal antibody titers in hemodialysis patients as a function of time since vaccinationTo determine factors influencing antibody kinetics (eg, age, prior or ongoing immunosuppression, medication, and prior vaccination history)To explore the relationship between antipneumococcal antibody titers and the incidence of pneumonia in hemodialysis patients and to extrapolate a possible cutoff for protection from pneumoniaTo evaluate the role of patients’ history (eg, underlying kidney disease) and clinical course (eg, prior hospitalizations) on pneumonia and vaccine response

## Methods

### Study Design

This is a prospective, multicenter, noninterventional study of vaccine efficacy in hemodialysis patients. All dialysis patients who are vaccinated against pneumococcal infection in accordance with RKI guidelines before enrollment will be eligible. Eligibility depends on the agreement of signing an informed consent allowing for data entry into the study electronic case report form (eCRF) and participation in the electronic quality registry, thus enabling data transfer from the patient’s Kuratorium für Dialyse und Nierentransplantation e.V. (KfH) electronic health record into the eCRF, titer assessments, and active follow-up observation. A minimum of 792 patients will be enrolled.

Participating sites will screen all hemodialysis patients at their outpatient dialysis clinic for eligibility. Eligible patients will be approached and informed by their physicians. If a patient agrees to participate in the study and signs an informed consent form (ICF), basic data regarding vaccination history, underlying disease, and so on will be entered or imported electronically into the study eCRF. Pneumococcal antibody titers will be drawn at baseline and every 3 months. For newly vaccinated patients, baseline titers will be drawn 4 weeks after vaccination. Deutsches Zentrum für Infektionsforschung (DZIF; English: German Center for Infection Research) clinical trial units (CTUs) will coordinate titer assessment schedules and inform the participating physicians of upcoming blood samplings. The samples will be taken on dialysis days from an already inserted-intravascular catheter. DZIF CTUs will actively follow up on study patients for 2-5 years after enrollment. This follow-up will include validation of all hospitalizations and deaths documented in the electronic registry to assess whether the primary end point (all-cause pneumonia) occurred. During months 25-30, only the primary end point will be recorded (ie, no blood samples will be taken). Additionally, dialysis units will be contacted every 6 months to assess if pneumonia occurred that did not require hospitalization. Blood samples will be stored frozen at DZIF CTUs, and titers will be analyzed at the end of this study. All therapies and diagnostics, including vaccinations, will be administered solely as part of the clinical routine and as recommended by appropriate guidelines (eg, RKI Ständige Impfkommission [STIKO] recommendations). Thus, Arzneimittelgesetz (AMG) does not apply to this study, and participating physicians do not require Good Clinical Practice (GCP) certification.

